**Methods:**

Eligible residents will be randomly assigned in a 1:1 ratio to either the intervention group (real-time ST and postoperative coaching) or the control group (traditional intraoperative hands-on teaching). This research adheres to the extended SPIRIT (Standard Protocol Items: Recommendations for Interventional Trials) statements for pilot RCTs and follows the intention-to-treat principle. Residents in both groups will perform 5 consecutive procedures under standardized intraoperative conditions. The primary outcomes are the Global Operative Assessment of Laparoscopic Skills (GOALS) score and the Non-Technical Skills for Surgeons (NOTSS). We hypothesize that the intervention group will show a 3- to 5-point improvement in the GOALS score compared with the control group. To achieve 0.8 statistical power, a *P* value <.05, and a 20% dropout rate in a definitive RCT, 12 residents per group are required. We present a pilot RCT with 5 residents per group. Challenges encountered during the trial will be reported, and amendments will be proposed to assess the need for a future definitive RCT.

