### Sample Size

This pilot RCT is designed to identify challenges and unforeseen pitfalls in conducting a proper RCT. Given the novelty of the topic and the resources required for an RCT, it is necessary to conduct a pilot study to assess the feasibility of a full-scale RCT.

The full RCT is designed as a superiority trial to demonstrate the superiority of telementored resident skill acquisition in the OR compared with standard training methods. Previous investigations have shown that the SD of the GOALS score is 2.5. We hypothesize that the intervention group will demonstrate significant clinical improvement in skills, as evidenced by a 3‐ to 5-point increase in the GOALS score relative to the control group. To achieve a statistical power of 0.8, a significance level (*P* value) of <.05, and to account for an expected dropout rate of 20%, 12 residents per group are required for an RCT.

This pilot study will include 5 residents in both the experimental and control arms (n=10). Residents will be stratified into 2 groups according to the number of prior LCs.

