### Statistical Analysis

The primary analysis will compare mean GOALS scores between the intervention and control groups. An independent-samples *t* test will be used for this comparison, provided that the assumption of normality is met; if normality is violated, the nonparametric Mann-Whitney *U* test will be applied. Effect sizes will be calculated using Cohen *d* to quantify the magnitude of the difference between groups and to inform sample size estimation for a future definitive RCT.

Secondary analyses will include comparisons of NOTSS scores between the intervention and control groups using the same statistical approach as that used for the primary outcome. Within-group improvement in technical performance across the training period will be assessed by comparing GOALS scores from the first to the fifth procedure using paired *t* tests. Participant satisfaction scores will be compared between groups using the Mann-Whitney *U* test, as these data are collected on an ordinal Likert scale.

Multivariate analyses will be conducted using linear regression models to examine the association between group allocation and GOALS scores while adjusting for potential confounding factors. Group allocation (intervention vs control) will be included as the primary predictor. Covariates will be selected a priori based on theoretical relevance and will include baseline surgical experience (defined as completion of 5‐10 vs 10‐20 prior LCs), baseline GOALS score from the first procedure, year of residency training, study site (Sandnessjøen vs Mo i Rana), and indicators of procedure complexity, including intraoperative findings and operative time.

Exploratory analyses will be performed to further characterize performance development and relationships between outcomes. Learning curves across the 5 procedures will be evaluated by examining trajectories of GOALS scores using repeated-measures ANOVA or mixed effects models, depending on the data structure and model assumptions. Subgroup analyses stratified by baseline experience level will be undertaken, and correlations between GOALS and NOTSS scores will be assessed to explore the relationship between technical and nontechnical performance.

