### Data Presentation

Continuous variables will be presented as mean (SD) for normally distributed data and as median (IQR) for skewed distributions. Categorical variables will be presented as frequencies and percentages. A *P* value <.05 will be considered statistically significant. Given the pilot nature, emphasis will be placed on effect sizes and CIs rather than *P* values alone. Descriptive statistics and data analysis will be performed using Microsoft Excel - Office 365 and IBM SPSS Statistics software (version 31.0; IBM Corp).

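### With 5 residents per arm, Cohen d without a small-sample correction overstates a non-zero effect by about 11% on average; Hedges g would remove this minor bias at no cost

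*Protocol article*

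**What the plan says.** Four places in the protocol article matter.

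- **Statistical Analysis** fixes the statistic: "Effect sizes will be calculated using Cohen" d, as the measure of how far apart the groups are. It also gives it a planning use: "to inform sample size estimation for a future definitive RCT". NOTSS is to be compared in the same way as GOALS.
- **Sample Size** fixes the pilot: "This pilot study will include 5 residents in both the experimental and control arms".
- **Data Presentation** sets the reporting weight: "emphasis will be placed on effect sizes and CIs rather than" P values alone. It gives mean (SD) for normally distributed data and "median (IQR) for skewed distributions".
- **Introduction**, in the list of specific pilot aims, includes preliminary effect sizes for refining the sample size of the full trial.

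The article does not say whether d is corrected for small samples. It does not use the name Hedges g.

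**The concern.** Cohen d divides the mean difference by the pooled SD. In small samples the reciprocal of the estimated SD is too large on average, so d is too far from zero on average whenever the true difference is not zero. The size of this bias depends only on the degrees of freedom, and it can be removed by a known factor. At ordinary trial sizes it is negligible; at 5 per arm it is about a tenth of the effect.

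The article gives this statistic a prominent place and intends to use it for planning, so the version that is unbiased under normality is the natural choice. At stake is a modest average overstatement of the standardized effect. The validity of the primary comparison is not in question.

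**Working it through.** **Inputs**

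- 5 residents per arm (Sample Size).
- SD of GOALS 2.5 and a hypothesized difference of 3 to 5 points (Sample Size), so the true standardized difference is 3/2.5 = 1.2 to 5/2.5 = 2.0.
- Assumptions: normal scores with equal variance, one summary value per resident, no losses. Degrees of freedom = 5 + 5 − 2 = 8.

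**The plan's own figure.** The article gives no figure for the bias of d. Its nearest figure is 12 per group for the definitive trial, including 20% dropout. A two-sided normal approximation at 3 points gives 11, and 11/0.8 rounds up to 14. One-sided at 3 points, or two-sided at 3.5 points, gives 9, and 9/0.8 rounds up to 12. So 12 can be reached, although the article does not say by which route. Nothing below depends on it.

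**Bias factor.** J(df) = Γ(df/2) / [√(df/2) × Γ((df−1)/2)]. The expectation of d is the true value divided by J, and Hedges g is J × d.

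For df = 8: Γ(4) = 6, √4 = 2, Γ(3.5) = 3.3234, so J = 6/(2 × 3.3234) = 0.9027 and 1/J = 1.108.

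| df | Situation | J | Average overstatement |
|---|---|---|---|
| 8 | 5 + 5 residents | 0.9027 | 10.8% |
| 7 | one resident lost | 0.8882 | 12.6% |
| 6 | two residents lost | 0.8686 | 15.1% |

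The last two rows apply because the Data Monitoring section specifies available-case analysis.

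**Expected values at 8 df.** True 1.2: 1.2/0.9027 = 1.33. True 2.0: 2.0/0.9027 = 2.22.

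**Simulation of 1,000,000 pilots at 5 per arm**

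| True value | Mean d | Median d | SD of d | Bias/SD | Mean g |
|---|---|---|---|---|---|
| 0 | 0.00 | 0.00 | 0.73 | 0.00 | 0.00 |
| 0.5 | 0.55 | 0.52 | 0.75 | 0.07 | 0.50 |
| 1.2 | 1.33 | 1.24 | 0.83 | 0.16 | 1.20 |
| 2.0 | 2.22 | 2.07 | 0.98 | 0.22 | 2.00 |

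At a true value of 1.2 the root mean squared error is 0.84 for d and 0.75 for g. So g is both unbiased and closer to the truth on this measure.

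**Scale of the imprecision.** An observed d of 1.2 at 5 per arm has an exact (noncentral t) 95% confidence interval of −0.20 to 2.54.

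**Unit of analysis.** Each resident performs five procedures. If all 50 scores were treated as independent (48 df), the overstatement would be only 1.6%. That would ignore clustering within residents, so it is shown only as a bound.

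**The case against.** The strongest reply is that the article never says d is uncorrected. It is a condensed document, the label Cohen d is often used loosely, and the exact variant may be set in an analysis plan that is not shown. This partly stands: the lack of a correction is the ordinary meaning of the name, not something the article states. But the article does choose an estimator by name, at a stated sample size and for a stated purpose, and a better one is available for a change of wording.

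The second reply is that imprecision dominates. This stands in full. The bias is at most about 0.22 of the sampling SD over the values examined, the median d is only 3–4% high, and the Limitations section already says that the small sample rules out firm conclusions on effectiveness. That makes the point minor. It is still worth acting on, because the bias can be removed and the imprecision cannot.

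A reader might infer three stronger things that the documents do not support:

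- **That the pilot's result is wrong on average whatever its use.** The bias is proportional and vanishes at a true difference of zero. It does not touch the raw difference, the t test, the P value or an exact interval for d.
- **That the definitive trial would typically be too small.** Putting the mean of d (1.33) into a two-sided t-test calculation at 80% power gives 10 per group, where 1.2 needs 12; 10 per group has about 72% power for a true 1.2. But this plugs in a mean, and the required size is a non-linear function of d. The median d of 1.24 still gives 12 per group, so those figures do not describe a typical pilot. The median g of 1.12 gives 14.
- **That the median (IQR) rule would stop readers from correcting d.** The correction needs only the degrees of freedom, which follow from the group sizes. The SD matters for a different purpose: recovering the effect in score points.

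**Conclusion.** The point holds as a minor, free improvement. Cohen d in its standard form, at 5 residents per arm, overstates a non-zero standardized difference by 10.8% on average, by 12.6% if one resident is lost and by 15.1% if two are. Over the hypothesized 3 to 5 points this moves a true 1.2 to an average of 1.33 and a true 2.0 to an average of 2.22.

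The conclusion assumes normal scores with equal variance, one summary value per resident, and no correction specified elsewhere. It does not amount to an error in the primary comparison. Sampling variation in a 10-resident estimate is several times larger than the bias and remains whichever version of the effect size is reported.

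**What to change.** In **Statistical Analysis**, replace Cohen d by Hedges g (d × 0.903 at 5 per arm, with the factor for the actual degrees of freedom if residents are lost) and its 95% confidence interval. Beside it, report the raw mean difference in GOALS and in NOTSS points, each with its confidence interval.

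In **Data Presentation**, always give the mean and SD per arm for both scores, with median (IQR) added where scores look skewed. This keeps the raw-scale inputs available for planning the definitive trial.

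The cost is a change of wording. The timeline puts data analysis in November 2026, so the change can be specified before then. The reported standardized effect becomes about 10% smaller (1 − 0.903 = 0.097), and no data collection or test changes. The revised text should not present g as a remedy for the imprecision of the pilot estimate.

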**Objective:**

We aim to conduct a pilot randomized controlled trial (RCT). Data collection will inform a future full-scale RCT evaluating whether real-time ST, combined with structured postoperative coaching, is superior to traditional on-site mentoring in developing laparoscopic cholecystectomy skills among surgical residents.

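### First-to-fifth improvement in GOALS is tested only within each arm, and no between-arm contrast in improvement is named (minor)

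*Protocol article*

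**What the plan says.** The Objective in the Abstract asks whether telementoring with coaching "is superior to traditional on-site mentoring in developing laparoscopic cholecystectomy skills among surgical residents". The Introduction states the hypothesis as a 3- to 5-point GOALS advantage over control.

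The Statistical Analysis section plans four analyses of GOALS:

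- **Primary:** "The primary analysis will compare mean GOALS scores between the intervention and control groups", by t test or Mann-Whitney test, with Cohen d. The procedure or procedures that enter the mean are not stated.
- **Secondary, within arm:** "Within-group improvement in technical performance across the training period will be assessed by comparing GOALS scores from the first to the fifth procedure", by paired t tests.
- **Regression:** "Group allocation (intervention vs control) will be included as the primary predictor". The covariates include the "baseline GOALS score from the first procedure". The procedure that supplies the outcome is again not stated.
- **Exploratory:** "Learning curves across the 5 procedures will be evaluated by examining trajectories of GOALS scores using repeated-measures ANOVA or mixed effects models". No arm-by-procedure term is named.

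The Sample Size section gives 5 residents per arm and a GOALS SD of 2.5. The Data Presentation section sets P<.05 as the threshold and puts the emphasis on effect sizes and CIs.

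**The concern.** The trial asks about development of skill relative to control. The one analysis that names a change from first to fifth procedure is done separately in each arm. A paired test asks whether the mean change in that arm differs from zero. It says nothing about whether the two changes differ from each other, and it makes no use of the randomised comparison.

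The practical risk lies in the reporting. With a P<.05 threshold, the results would carry one verdict per arm for improvement. A reader who sees a significant gain in one arm and not in the other may take that as a difference between arms. With 5 residents per arm, such a split is common even when both arms learn equally.

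The Introduction also wants preliminary effect sizes for the definitive trial. Two within-arm P values do not supply one for differential improvement.

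**Working it through.** The plan gives no figure for this contrast, so there is none to reproduce.

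**Inputs.** From the document: n = 5 per arm, GOALS SD 2.5, threshold .05. Assumed, because the document does not give them: two-sided testing, normal data, SD of the first-to-fifth change 2 to 3, and an equal true gain of 2 or 3 points in both arms.

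The assumed SD of change is consistent with the stated SD. If both scores have SD 2.5 and correlation r, the SD of change is 2.5 × √(2(1 − r)). This is 2.96, 2.50 and 1.94 at r = 0.3, 0.5 and 0.7.

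**Step 1: power of one paired test.** Noncentral t with 4 df, noncentrality = (gain / SD of change) × √5, critical value 2.776.

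**Step 2: chance that exactly one arm is significant when the true gains are equal.** The arms are independent, so this is 2p(1 − p), where p is the power from step 1.

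| True gain, both arms | SD of change | Noncentrality | Power p | 2p(1 − p) |
|---|---|---|---|---|
| 2 | 2 | 2.24 | 0.40 | 0.48 |
| 2 | 2.5 | 1.79 | 0.28 | 0.40 |
| 2 | 3 | 1.49 | 0.21 | 0.33 |
| 3 | 2 | 3.35 | 0.71 | 0.41 |
| 3 | 2.5 | 2.68 | 0.53 | 0.50 |
| 3 | 3 | 2.24 | 0.40 | 0.48 |

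Power runs from 0.21 to 0.71 and the chance of a split verdict from 33% to 50%. Half of these splits would favour telementoring.

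**Step 3: check by simulation.** 100,000 runs per setting, 5 per arm, score SD 2.5, equal true gains.

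| True gain, both arms | r = 0.3 | r = 0.5 | r = 0.7 |
|---|---|---|---|
| 2: split verdict | 34% | 40% | 49% |
| 3: split verdict | 49% | 50% | 39% |
| 5: split verdict | 32% | 17% | 3% |
| Direct between-arm test of change, any of these gains | 5% | 5% | 5% |

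The split becomes less frequent once gains are large enough for both arms to be significant nearly always. The 33% to 50% range therefore belongs to gains of 2 to 3 points.

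**Step 4: what the direct contrast can deliver.** The 95% CI half-width for the between-arm difference in change is 2.306 × SD × √(2/5), with 8 df:

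- SD 2: 2.306 × 2 × 0.632 = 2.9 points
- SD 3: 2.306 × 3 × 0.632 = 4.4 points

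Power to detect a true extra gain of 3 points is 29%, 39% and 58% at r = 0.3, 0.5 and 0.7. For 5 points it is 65%, 79% and 95%.

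**The case against.** The strongest reply is that the protocol never makes the faulty inference. The paired tests are secondary, are labelled as within-group, and are nowhere offered as evidence of superiority. Whether residents improve over five procedures is a fair descriptive question. This stands. The 33% to 50% figure is not an error rate of the plan; it applies only if someone reads split P values as an arm difference.

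The second reply is that the between-arm question is handled elsewhere. This stands in part.

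- The primary test uses the randomisation and addresses the stated hypothesis, but it compares a level of GOALS and not a gain.
- The regression could compare development if its outcome were a later score adjusted for the first. The outcome procedure is not stated. With one score per resident, the seven listed predictors and an intercept would leave at most 10 − 8 = 2 residual degrees of freedom.
- The trajectory models could supply the contrast but are exploratory, and the form of model is left open.

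A reader might infer that the plan makes no randomised comparison of skill at all, or that it will claim superiority from the paired tests. The document supports neither reading.

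The third reply is that an unnamed interaction term is detail for an analysis plan not shown here. On its own, that would be right. The point rests on what the article does fix: a within-arm test is named for improvement and a between-arm one is not.

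Finally, change from procedure 1 is not clearly a better measure of effect, because procedure 1 is already done under the allocated mentoring. This stands, and it limits the fix to a supplement.

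**Conclusion.** The point holds in a narrow form and is minor. Improvement from the first to the fifth procedure is tested only inside each arm, and no between-arm contrast in improvement is named. Within-arm tests cannot answer whether telementored residents improve more.

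If the two results were read against each other, a split verdict would arise in about 33% to 50% of trials with no true difference in gain, against about 5% for a direct test. That size rests on equal gains of 2 to 3 points, an SD of change of 2 to 3, normal data and two-sided testing. None of these is given in the document.

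The consequences are limited by the secondary status of the tests, the between-arm primary comparison, the stated emphasis on effect sizes and CIs, and the protocol's own statement that so small a pilot cannot settle effectiveness.

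**What to change.** Keep the primary comparison as it is. Among the secondary analyses, report one of these with a 95% CI:

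- the between-arm difference in first-to-fifth change in GOALS; or
- the arm-by-procedure term of the mixed model already listed, with a random effect for resident.

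Give the within-arm changes descriptively (mean and SD) without P values.

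State two limits beside the result. The first procedure takes place under the allocated mentoring, so the contrast omits any immediate effect. With 5 per arm the interval will be wide, about ±2.9 to ±4.4 points under the assumed SDs, so it serves planning of the definitive trial and not a conclusion about benefit.

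The cost is a few lines of analysis text. No new data are needed, and analysis is not scheduled until November 2026.

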### Recruitment Procedures

The residents will be randomized into 2 groups. Residents in the control group will receive traditional OR supervision throughout all 5 consecutive procedures, with on-site mentoring by an experienced surgeon. The intervention group will receive guidance from a remotely located expert via live stream during 5 consecutive procedures.

Recruitment of research participants (surgical residents) will primarily occur at their local hospitals. During 2024 and 2025, all patients referred to hospital surgical departments with a diagnosis of gallstone disease and scheduled for LC will be assessed for inclusion. Study residents will be scheduled for 5 LCs within 3 days. If not enough residents are recruited at the local hospitals, recruitment efforts will be extended to include residents from other hospitals.

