### Participant Timeline

To ensure transparency and adherence to reporting standards for RCTs, according to the Consolidated Standards of Reporting Trials (CONSORT), the trial design is summarized in the CONSORT flowchart in Figure 4. The timeline of surgical residents’ inclusion in both groups is shown. Residents who consented to inclusion will be informed of randomization 1 week before the planned procedures. In addition to the planned stepwise procedure description, standardized information on communication during the telementoring procedure will be provided.

This protocol follows the SPIRIT 2025 guidelines for clinical trial protocols. A complete SPIRIT checklist is provided as Checklist 1.

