#### Preprocedure Setup and Coaching

Before commencing the surgical procedure, a standardized setup phase of approximately 10 to 15 minutes is implemented. Key steps to ensure operational readiness include the following: the resident confirms connectivity to the telementoring system with the remote mentor; a bilateral communication check of the audio headset is performed, and the video feeds from both the laparoscopic and external OR cameras are verified by the telementor. This phase concludes with a brief preoperative discussion to review the surgical plan and anticipate potential challenges.

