#### Intraoperative Telementoring

During the operation, the telementor provides real-time guidance by observing a high-definition video stream and maintaining continuous audio communication via a wireless headset. When anatomical clarification is required, the telementor activates the telestration mode. This process involves the following:

The procedure is temporarily paused using a specific “stop word” command from the mentor.A static image is captured from the laparoscopic feed.The mentor annotates the image using lines, circles, or arrows to highlight relevant anatomical structures, dissection planes, or areas of concern.The resident confirms their understanding of the annotations before the procedure is resumed.

The Lapco communication protocol, an integral component of the Lapco standardized teaching framework, follows the “6 steps”: stop → identify → explain → instruct → check → assess. The steps are defined as follows:

Stop. The telementor (trainer) initiates the sequence by pausing the procedure completely with the stop signal, often when the telementee (trainee) encounters difficulty or reaches a critical juncture, to gain the telementee’s full attention and prevent errors.Identify. The telementor asks the telementee to clearly identify the specific problem, concern, or relevant anatomical structure to ensure mutual understanding of the issue.Explain. The telementor provides a brief explanation of the underlying principle or rationale behind the next required action, connecting theory to practice.Instruct. Clear, concise instructions are provided to the telementee on how to perform the next step correctly.Check. The telementee verbally confirms that they understand the instructions and are prepared to execute them safely by repeating the instructions provided in step 4.Assess: After the telementee attempts the maneuver, the telementor provides an assessment and determines whether the procedure can proceed safely without further instructions or whether the on-site surgeon should assume control of the procedure. The latter should be avoided to maximize learning.

A local consultant surgeon is scrubbed for all procedures and assists as the camera-holding surgeon during the laparoscopic procedure but does not provide teaching input unless patient safety requires intervention.

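### The supporting adjusted GOALS regression conditions on variables measured after randomization, including a procedure-1 score labelled as baseline; the unadjusted primary analysis is not affected

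*Protocol article*

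**What the plan says.** Under Statistical Analysis, the primary analysis is an unadjusted comparison of mean GOALS by t test or Mann-Whitney test. Cohen d is to be calculated with it, to inform the size of a definitive trial. A linear regression of GOALS on arm follows, with the stated purpose of "adjusting for potential confounding factors". Its covariates are said to be chosen a priori. Besides prior-experience stratum they are "baseline GOALS score from the first procedure, year of residency training, study site" and "indicators of procedure complexity, including intraoperative findings and operative time".

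The timing of these measurements follows from other sections:

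- Participant Timeline: "Residents who consented to inclusion will be informed of randomization 1 week before the planned procedures".
- Recruitment Procedures, telementoring arm: "The intervention group will receive guidance from a remotely located expert via live stream during 5 consecutive procedures".
- Recruitment Procedures, control arm: "Residents in the control group will receive traditional OR supervision throughout all 5 consecutive procedures".
- Preprocedure Setup and Coaching, telementoring arm only: "This phase concludes with a brief preoperative discussion to review the surgical plan and anticipate potential challenges".
- Primary Outcomes: GOALS is scored from the video of every procedure, the first included.
- Intraoperative Telementoring, on telestration: "The procedure is temporarily paused using a specific" stop command from the mentor.
- Intraoperative Mentoring, control arm: the mentor may take over the instruments for a time.

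No GOALS assessment before randomization, or without mentoring, is described.

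**The concern.** A covariate in a randomized comparison is safe when allocation cannot have changed it. Three on this list are observed after allocation, while the allocated mentoring is under way.

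- **GOALS at procedure 1** is labelled as baseline but is one of the five measurements of a primary outcome. The Introduction's case for telementoring rests largely on mechanisms that act during the operation (shared view, structured communication, undivided attention), so the plan's own reasoning allows an effect at the first case.
- **Operative time** can be lengthened by telestration pauses in one arm and altered by instrument takeover in the other. It also overlaps with the efficiency subscale of GOALS.
- **Intraoperative findings** could mean anatomy or existing inflammation, which mentoring cannot change, or events such as bleeding or perforation, which it can. The text does not say which.

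With such covariates in the model, the arm coefficient no longer estimates the total effect of telementoring with coaching. A reader who sees it beside the unadjusted difference could take the gap for confounding that had been removed, when part of it is treatment effect.

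**Working it through.** **Figures in the plan.** The plan gives no figure for the adjusted model. The check uses the hypothesized 3- to 5-point effect and the pilot size of 10 residents (Sample Size). The 12 per group for the definitive trial rests on an unadjusted comparison and does not enter. The stated SD of 2.5 cancels in steps 1 to 3.

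**Assumptions, not in the documents.** Within-resident correlation (ICC) of 0.3, 0.5 or 0.7, equal across procedures; common SD; f = share of the effect already present at procedure 1.

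**Step 1, identity.** In least squares with a randomized arm:

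adjusted coefficient = total effect − b × (effect at procedure 1),

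where b is the within-arm slope of the outcome on the procedure-1 score. If the outcome is the mean of procedures 2 to 5, b = ICC, and for a total effect D the coefficient is D × (1 − ICC × f).

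| D | f | ICC 0.3 | ICC 0.5 | ICC 0.7 |
|---|---|---|---|---|
| 3 | 0 | 3.00 | 3.00 | 3.00 |
| 3 | 0.5 | 2.55 | 2.25 | 1.95 |
| 3 | 1 | 2.10 | 1.50 | 0.90 |
| 5 | 0.5 | 4.25 | 3.75 | 3.25 |
| 5 | 1 | 3.50 | 2.50 | 1.50 |

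Example: 3 × (1 − 0.7 × 0.5) = 1.95.

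**Step 2, outcome as the mean of all five.** The covariate is then part of the outcome, and b = (1 + 4 × ICC)/5 = 0.44, 0.60, 0.76. For a constant 3-point effect: 3 − 3b = 1.68, 1.20, 0.72.

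**Step 3, an effect that grows.** With effects of 1, 2, 3, 4 and 5 points at the five procedures, the mean is 3 and the effect at procedure 1 is 1. The coefficient is 3 − b = 2.56, 2.40, 2.24, a loss of about 15% to 25%.

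**Step 4, operative time.** Simulation with 200,000 residents, total SD 2.5, ICC 0.5, a 3-point effect on the mean of procedures 2 to 5, and assumed operative time 2 minutes shorter per GOALS point with residual SD 8 minutes. Pauses add either 0 or an assumed 10 minutes in the telementoring arm.

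| f | Added pauses | Unadjusted | + time | + time and procedure-1 GOALS |
|---|---|---|---|---|
| 0.5 | 0 min | 3.01 | 2.49 | 2.06 |
| 0.5 | 10 min | 3.00 | 3.43 | 2.60 |
| 1 | 0 min | 3.00 | 2.44 | 1.38 |
| 1 | 10 min | 3.01 | 3.39 | 1.91 |

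Time alone can pull the coefficient down or push it up.

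**Step 5, number of coefficients.** Intercept, arm, experience, procedure-1 GOALS, year, site, findings and time make 8, counting year and findings as one term each. With one row per resident, 10 − 8 = 2 residual degrees of freedom remain (two-sided 5% critical t 4.30), against 8 for the two-group comparison (2.31).

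**The case against.** The strongest reply is that this model is not the one that counts. The primary comparison is unadjusted, and the Cohen d named for planning the definitive trial belongs to it. The regression is given no role in sizing, Data Presentation puts effect sizes and CIs ahead of P values, and Limitations disclaims definitive conclusions. All of this stands, and it sets the severity. A reader might infer that the primary result, or the planning of the definitive trial, is biased; the documents do not support that.

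The loss may also be small. Postoperative coaching, a core part of the intervention, first takes place after procedure 1, so its effect is not removed by this route. If nothing acts at procedure 1, nothing is lost. This too stands: 2.1 to 0.9 is the far end of a range that starts at no loss.

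Two further corrections hold. Only procedure-1 GOALS is labelled as baseline; the other two are called complexity indicators, though they enter the same adjustment. And some intraoperative findings are legitimate measures of case difficulty. Unfavorable incidents are handled separately under Patient-Related Outcomes and Complications, so it goes too far to treat every finding as a consequence of mentoring.

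Finally, the unit of analysis is not fixed. Operative time and findings vary by procedure, which may imply up to 50 rows (10 residents × 5); the 2 degrees of freedom apply only at one row per resident.

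None of this makes procedure-1 GOALS a baseline, or operative time a confounder of a randomized comparison.

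**Conclusion.** The adjusted GOALS model is wrongly specified as written, and its arm coefficient does not estimate the total effect of the intervention. The part due to procedure-1 GOALS is ICC × f of the effect on procedures 2 to 5: nothing at f = 0, 15% to 35% at f = 0.5, and 30% to 70% at f = 1, for ICC 0.3 to 0.7. Both quantities are assumptions; the documents give neither.

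It is tempting to say that the model always shrinks the effect. That holds for procedure-1 GOALS when some benefit is already present at that case. It does not hold for operative time, where the simulated 3-point effect moved to between about 2.4 and 3.4. For intraoperative findings, no direction or size can be given until they are defined.

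This is a should-fix: a clear error in a pre-specified supporting analysis, with the primary comparison and the effect size used for sizing unaffected.

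**What to change.** In the Statistical Analysis section:

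1. Remove procedure-1 GOALS and operative time from the adjusted model.
2. Restrict complexity indicators to patient characteristics that mentoring cannot change, such as pre-existing inflammation, adhesions or anatomy, and name them.
3. Adjust for few variables fixed before randomization, chiefly the experience stratum.
4. Keep procedure 1 as an outcome time point, as the repeated-measures or mixed model planned in the same section already allows.

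The cost is a change of wording, with no new data and no change to conduct. Ethical Considerations requires protocol modifications to go to the ethics committee before implementation, so a short submission is needed. Analysis is scheduled for November 2026, and the change should be dated before then.
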